### Ethical Considerations

Ethics approval will be sought by January 2024 for an international and multicentric randomized control trial involving tertiary care centers in Canada, the United Kingdom, and Belgium. Only participants who are adults and able to consent will be recruited for this study. This study presents minimal risks for participants, as only behavioral therapy will be provided in the study procedures: there will be no use of approved or unapproved drugs, biologics, food, or dietary supplements. This study does not evaluate the safety or effectiveness of a device. No protected health information will be collected or placed into electronic medical records. No compensation or incentive is planned to be provided at this time.

### Data Management Plan

All data will be collected in an electronic format. In the unanticipated event that data cannot be collected electronically, the same information will be collected via pen and paper, transferred to Excel, and the paper format will be destroyed at the earliest opportunity. All collected data will be strictly confidential, within the limits established by law, and a numerical code will identify each participant. Data will be recorded in the cloud of the University of Montreal, specially developed for research purposes, and only the team members will have access. Furthermore, all data will be conserved, for a minimum period of 7 years, after which they will be destroyed. None of the potential scientific publications or communications related to the study will contain participant-identifiable information. The researchers and the research assistants will only consult data. No facial recordings or sensitive or medical information will be held on the websites used in the study. Only the name, email address, and information about the affected side of the facial palsy (for duplication of the unaffected side purpose) and preference about sound level (with or without sound) will appear. Moreover, both websites use the latest versions of tools and information components, such as long time support, which offer support and security updates regularly, and a specialized technical team will ensure security updates and support for maximal security.

## Results

The inclusion will start in late 2024, and data collection is anticipated to be completed over 3 years by 2027. Therefore, the last patient will have their final follow-up (T3) in 2028. Data analysis will be completed in 2028-2029. The results will be published in 2030.

## Discussion

### Main Study Findings

The primary objective of this protocol is to compare the potential effects of adjunctive mirror therapy with the gold standard fNMR for facial function and rehabilitation in cases of nonflaccid facial paralysis. In particular, this study aims to evaluate the impact of combined therapy versus fNMR alone on participants’ facial symmetry, facial synkinesis, quality of life, motivation, and treatment adherence.

### Comparison With Prior Work and Scientific Value of This Work

A recent Delphi study has confirmed the significance of fNMR and mime therapy in treating patients with various types of peripheral facial paralysis [39]. While mirror therapy was not unanimously agreed upon for inclusion at that time, subsequent data published after the study indicated that mirror therapy, when initiated a few days after the onset (10-14 days) of Bell palsy, had notable benefits. These benefits included a significant improvement in facial symmetry, quality of life, and a reduction in the development of synkinesis [23]. Similar positive outcomes have also been observed in patients with facial palsy after acoustic neuroma resection and in those who underwent lengthening temporalis myoplasty surgery [17,24]. However, despite these findings, there is a dearth of research examining the potential effects of mirror therapy in patients with peripheral facial palsy experiencing delayed recovery and sequelae at least 3 months after the onset, compared to more traditional therapies like fNMR.

Irrespective of the etiology and group allocation (fNMR vs mirror therapy), our hypothesis posits that all patients with peripheral facial palsy enrolled in this study will experience improvements in facial symmetry, synkinesis, and quality of life [11,23,40]. Drawing on previous studies [23,41] and considering that mirror therapy appears most beneficial when initiated early, we anticipate mirror therapy to have greater benefits for patients in the paretic phase (3-6 months after onset), particularly in terms of restoring facial symmetry. Patients presenting with synkinesis at the time of recruitment should experience a decrease in synkinesis in the fNMR group, as indicated by several previous studies [4,5,7,13,14]. Similarly, a decrease in synkinesis is expected in the mirror therapy group, but no significant differences between the 2 groups are anticipated. Moreover, in line with previous findings [5,23], we expect both the fNMR and mirror therapy groups to demonstrate improvements in self-reported quality-of-life measures. Additionally, motivation is crucial in achieving positive therapy outcomes [42] and will be specifically assessed in this study. The hypothesis of greater motivation with mirror therapy is based on a previous study where patients reported that performing facial exercises while viewing a symmetrical face aided them as it represented their desired goal [41]. On the contrary, some patients may experience emotional responses when confronted with a face they perceive as “lost” due to facial paralysis.

Finally, we anticipate that patients in the mirror therapy group will exhibit better treatment adherence compared to those undergoing fNMR alone. Adherence to facial retraining has been shown to be influenced by various factors, including time constraints due to other daily activities and accessibility to the training facilities [43]. Facial therapists often overestimate their patients’ commitment to the facial rehabilitation process, with data indicating that only 30% of patients fully comply [43]. Nonadherence to therapy can impact treatment outcomes, highlighting the importance of measuring adherence in this study. Objective measures of adherence using metadata will be used, providing strength compared to relying solely on subjective measures of compliance. Subjective measures of compliance (such as patient questioning) may be influenced by patients’ memory or perceptions [44]. Furthermore, the postpandemic shift toward telehealth for service delivery may facilitate adherence [44]. In this study, we will document whether participants received care via telehealth and examine whether this factor appears to influence compliance.

### Strengths and Limitations

The primary strength of this protocol lies in its international multicentric collaboration, which will facilitate the examination of a substantial number of participants representing diverse etiologies of peripheral facial nerve palsy (n=90, with 45 patients per group). The randomized controlled trial design used in this study allows for assessing the potential additional benefits of incorporating mirror therapy into the rehabilitation of PFP. This investigation has the potential to contribute to an evidence-based approach for clinicians involved in the care of these patients.

However, the study design does have certain limitations. First, it is not feasible to blind both the patients and treating clinicians to the assigned conditions, which could introduce bias in terms of motivation and perception of treatment efficacy. To mitigate these risks, blinded judges will be involved in assessing participants, and therapists will use a standardized feedback approach in both therapy sessions and assessments. Additionally, using Emotrics will allow for more objective facial metrics at each assessment time point [33,45]. Second, the inclusion of paretic patients in the study poses a potential confounding factor due to the occurrence of spontaneous recovery in certain cases of facial palsy [3]. However, the large number of participants and their enrollment at least 3 months after the onset of symptoms should help mitigate potential biases. It is worth noting that in Bell palsy, the most common cause of PFP, approximately 70% of patients experience full recovery within 3 months of onset [3]. The advantage of including patients across such a broad timeframe (3-12 months after onset) is to recruit a cohort that is as representative as possible of the clinical reality of facial rehabilitation in different countries.

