## Introduction

### Background

Peripheral facial palsy (PFP) with sequelae is a debilitating condition that can significantly impact a patient’s quality of life due to functional, social, and psychological factors [1]. Facial asymmetry and the inability to express emotions and smile adequately can make communication challenging, leading to high levels of social problems, frustration, anxiety, and depression [1]. In nonflaccid facial palsy, patients may have hyperkinesis, muscle contracture, and synkinesis, which can affect normal activities such as drinking, eating, and articulating and can cause embarrassment and, in some cases, facial pain [2,3]. Therefore, providing adequate interventions to help patients deal with these issues is essential. Physical therapy is a type of nonsurgical treatment shown to help manage the sequelae previously mentioned in patients with nonflaccid chronic peripheral facial palsy [4]. Optimal facial rehabilitation modalities could also differ depending on the stage of nonflaccid PFP [5]. Although there are no generally accepted guidelines for the different stages, some authors define the paretic phase as recovery from 3 to 6 months after onset, while the early synkinetic phase would be defined as 6 to 9 months after onset [5,6]. The chronic synkinetic phase would begin at 9 months after onset, as defined by Beurskens et al [7].

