### Recruitment and Compensation

As determined, thanks to a power calculation measure based on Martineau et al [22] to reach a power of 0.8 with a size effect of 0.6 and an α of .005, 90 patients with peripheral facial palsy of diverse etiologies in the paretic (n=30), early synkinetic (n=30), or chronic synkinetic phase (n=30) will be recruited to the study. They will then be randomized into 2 groups, mirror therapy plus fNMR or fNMR alone, by computerized block randomization. No compensation or incentive is planned to be provided at this time. Recruitment is planned to be conducted in 3 tertiary care centers (hospitals) in Canada, England, and Belgium (Hôpital Maisonneuve-Rosemont, Queen Victoria Hospital, and Sint-Augustinus GZA Hospital, respectively). A telehealth option will be available for the participants via institutionally secured platforms.

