### Statistical Analysis

As mentioned, a power calculation was done based on a previous study [23] for the primary outcome (changes from baseline to 6 months). Every measure of facial symmetry and synkinesis will be judged by 3 assessors, blinded to group assignment. Intraclass correlation coefficients will be calculated to ensure interrater reliability, and the resulting means of the assessors’ findings will be used for further statistical analysis. We will first gather descriptive statistics to provide summary data. Then, for continuous variables (Emotrics measurements, Sunnybrook global score, FNGS 2.0 global scores, FACE score, FDI, and intrinsic motivation inventory), a mixed model analysis with patients as random variables and time+group assignment as fixed variables will be considered, with auto-regressive covariance structure, given the structure of the time points for the assessments. Comparison between the timing of recruitment after PFP onset (3-6 months after onset vs 6-9 months vs 9-12 months) and outcomes at T2 and T3 will be specifically measured using multilevel analysis. Kruskal-Wallis analyses will be considered for ordinal variables (synkinesis subscores, symmetry subscores, and motivation subscores). Finally, chi-square analysis will be considered for dichotomous variables (adherence yes or no). Data will be encoded with Excel sheets, and SPSS (IBM Corp) will probably be used for statistical analysis.

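### Spontaneous recovery in paretic patients is named as a possible confounder, yet the stated main model has no term for onset phase, so the between-arm comparison gives up some precision and leaves chance imbalance uncorrected

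*Protocol article*

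**What the plan says.** Strengths and Limitations (Protocol article) states that "the inclusion of paretic patients in the study poses a potential confounding factor due to the occurrence of spontaneous recovery". The mitigation follows directly: "the large number of participants and their enrollment at least 3 months after the onset of symptoms should help mitigate potential biases". Background describes the same window in terms of recovery: "some authors define the paretic phase as recovery from 3 to 6 months after onset".

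Statistical Analysis gives the model for the continuous outcomes: "a mixed model analysis with patients as random variables and time+group assignment as fixed variables will be considered", with an autoregressive covariance. No onset or phase term is listed. Onset timing, in bands of 3-6, 6-9 and 9-12 months, enters only through a separate multilevel analysis against outcomes at T2 and T3. The primary outcome is the change from baseline to 6 months.

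Recruitment and Compensation sets the phase quotas: patients "in the paretic (n=30), early synkinetic (n=30), or chronic synkinetic phase (n=30) will be recruited to the study". Allocation is by computerised blocks, and the section does not say whether blocks are formed within phase. Eligibility Criteria requires onset 3 to 12 months earlier, so onset timing is known for everyone enrolled.

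**The concern.** The article identifies a baseline characteristic that may drive change over the treatment period, records it for every patient and fills a third of the sample with the group concerned. It then states a main model that does not use it. The two remedies offered do not replace adjustment. Enrolment from month 3 still admits patients throughout the window that the article itself associates with recovery. A larger sample makes chance imbalance smaller, but does not take phase out of the residual variance.

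At stake is the efficiency of the main between-arm answer. Variation that phase explains stays in the error term, and if one arm happens to receive more paretic patients, the estimated mirror-therapy effect moves with that excess.

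**Working it through.** **1. The plan's own figure.** Recruitment and Compensation states the inputs "to reach a power of 0.8 with a size effect of 0.6 and an α of .005" and a total of 90. With a two-sample t test and d = 0.6:
- two-sided .05: 45 per arm, N = 90, power 0.804;
- two-sided .005: 76 per arm, N = 152, and power at 45 per arm is 0.49.

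So .05 reproduces N = 90 and the printed .005 does not. That is a separate matter. The power figures below use two-sided .05 because it matches the planned sample size.

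**2. Variance explained by phase (assumption).** The documents give no figure for the extra paretic gain. Let it be g, in SDs of the 6-month change. With a paretic share of 1/3, R² = g² × (1/3) × (2/3). Adjusting scales the residual SD by √(1 − R²), so the effective d is 0.6/√(1 − R²).

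**3. Linear months instead of phase.** Suppose onset is uniform over 3-12 months and the extra gain is a step at 6 months. Mean onset is 4.5 months for paretic patients and 9 for the rest. The covariance has size (2/9) × 4.5 = 1, the variance of months is 81/12 = 6.75 and the variance of the step is 2/9. The squared correlation is 1/(6.75 × 2/9) = 0.667, so a linear term captures two thirds of R².

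| g (assumed) | R², phase | Power, phase | R², linear months | Power, linear months |
|---|---|---|---|---|
| 0 | 0 | 0.80 | 0 | 0.80 |
| 0.25 | 1.4% | 0.81 | 0.9% | 0.81 |
| 0.50 | 5.6% | 0.83 | 3.7% | 0.82 |
| 0.75 | 12.5% | 0.85 | 8.3% | 0.84 |
| 1.00 | 22.2% | 0.89 | 14.8% | 0.86 |

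The few degrees of freedom spent on the covariate are ignored.

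**4. Chance imbalance, if blocks ignore phase.** The number of paretic patients in one arm is then hypergeometric (90 patients, 30 paretic, 45 drawn), with SD 2.25. The between-arm difference in paretic share has SD 2 × 2.25/45 = 0.10. A split of 18:12 or worse has probability 0.263, and 20:10 or worse 0.043. An 18:12 split shifts the unadjusted contrast by g × 6/45, which is 0.03 SD at g = 0.25 and 0.13 SD at g = 1.0, against a planned effect of 0.6 SD.

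**5. Which terms matter.** Four visits were simulated (1,500 replicates; patient effect plus autoregressive errors with known covariance; 0.6 SD effect at 6 months; paretic patients gaining an extra 1 SD, here in within-phase SDs).

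| Model | SD of 6-month contrast | Power |
|---|---|---|
| Group-by-visit, no phase | 0.231 | 76.7% |
| plus phase, main effect only | 0.231 | 77.1% |
| plus phase and phase-by-visit | 0.207 | 81.7% |

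Spontaneous recovery is a difference in slope, so a main effect of phase adds almost nothing. In the additive time-plus-group model, the single group coefficient averaged about 0.35, not 0.6, because it pools all visits including baseline. It gives no 6-month contrast. With no treatment effect, rejection rates were 4% to 6% in every model.

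**The case against.** The strongest case against is that nothing here is an error. A randomised comparison without covariates is valid, its standard error already allows for chance imbalance, and the simulation shows no inflation of the type I error. The article condenses a fuller plan, describes the model as one to be considered, and may leave covariates to an analysis plan that is not shown.

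The mitigation also has some substance. The article says that about 70% of Bell palsy patients recover fully within 3 months, and eligibility requires a grade of 4 or 5 from month 3 onward, so early recoverers are screened out. It calls spontaneous recovery only a potential factor in certain cases and quantifies no gradient. Onset timing is not ignored either: the multilevel analysis covers T2, the primary time point, and the Abstract lists stage among the objectives.

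Much of this stands. It limits the point to efficiency and makes its size unknown. Two parts do not dispose of it. First, the article does state the fixed terms and does state its mitigation, and adjustment appears in neither. Second, the timing analysis is described as relating recruitment timing to outcome. The text does not say whether group enters it, and does not tie it to the between-arm estimate.

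**Conclusion.** The point holds as a modest, nearly free improvement in precision. A named prognostic factor that is known for everyone is absent from the stated main model. Under an assumed extra paretic gain of 0.25-1.0 SD, power rises from 0.80 to 0.81-0.89 with phase as bands, or to 0.81-0.86 with linear months under uniform onset. At the low end the gain is negligible.

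A reader might infer more from the article's own word, confounding: that the between-arm result will be systematically biased or its error rate wrong. The documents do not support this, because allocation is randomised. A reader might also take the 26% chance of an 18:12 or worse split as a property of this trial. It holds only if blocks are not formed within phase, which the article leaves open. If blocks are formed within phase, imbalance between phases largely disappears, but the precision argument remains.

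**What to change.** In Statistical Analysis, add to the mixed model for the facial outcomes: onset phase (the three recruitment bands, or months since onset in a form that allows non-linearity), its interaction with visit, and a group-by-visit term. Take the adjusted group contrast at 6 months as the primary between-arm estimate. In Strengths and Limitations, cite this adjustment as the mitigation in place of reliance on the number of participants.

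The cost is a sentence or two and a few degrees of freedom. No new data are needed, since onset timing is already collected for eligibility and the phase quotas. The return is small if phase turns out to be weakly prognostic.

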### Conclusions

By comparing treatment modalities such as fNMR and mirror therapy within the scope of this international study, clinicians can gain valuable insights into effective approaches for addressing specific facial sequelae in patients. Understanding which modalities may be more effective at different stages of PFP is important for the field. Moreover, this study has the potential to shed light on the impact of motivation and treatment adherence on treatment outcomes.

## Abbreviations

FACE: Facial Clinimetric Evaluation
FDI: Facial Disability Index
FNGS 2.0: Facial Nerve Grading System 2.0
fNMR: facial neuromuscular retraining
MEPP: Mirror Effect Plus Protocol
PFP: peripheral facial palsy
